#### Data estimation up to the 18th year of life

Costs and outcome data of the reduced sample up to the 18^th ^year of life will be estimated, based on 1) empirical costs and outcomes up to five years of life; 2) parent estimations by means of a questionnaire; and 4) a matched sample (n = 250) of 18-year old twin children, of whom NTR data referring to the past will be studied. The sample from the NTR will be chosen such that their past health at five years of age matches with the health status of the children of the reduced sample who will have an average age of five years. If empirical data are missing, data will be obtained by means of literature and/or expert opinion. Based on these data inputs, a prognostic model - the TwinSing model - will be developed.

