## Methods/Design

### Design

A retrospective multi-centre (n = 5) cohort study will be performed, in which a representative sample of IVF twin children will be compared with a representative sample of IVF singletons with respect to mortality, health outcomes, HRQoL and costs from birth up to five years of life. Subsequently, future costs and health outcomes up to 18 years of life will be modelled. Input for the model will be based on the empirically collected data up to five years of life, existing databases, literature and expert opinion.

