#### Development TwinSing model

A prognostic model will be developed which estimates the short and long-term costs and health outcomes of IVF singletons and IVF twin children. The structure and modelling method of the TwinSing model will be determined in close cooperation with experts in the project team and the participating centres. We expect that a Markov model will best suit the data; however, the final decision regarding which modelling method to use will be made after data become available.

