#### Short and long-term cost-effectiveness of SET strategies versus DET strategies

The TwinSing model will be linked to a short-term Markov model developed at the University Hospital Maastricht [32], that compared seven embryo transfer strategies varying from three cycles SET to three cycles DET and several combination strategies. Parameter values were based on data from a large randomised controlled trial in which patients who started their first IVF cycle in the Maastricht University Medical Centre were included.

The economic evaluation will be performed from both the societal and the health care perspective and the time horizon will be 18 years. Cost and benefits occurring after one year will be discounted according to national guidelines [61].

The ultimate model - in which the short-term Markov model and the TwinSing model have been integrated - will enable the estimation of the cost-effectiveness of SET strategies versus DET strategies, expressed as the additional costs per life year gained and the additional costs per QALY. The cost-effectiveness will be analysed using a short term time frame (1-year) and a long term time frame (5 and 18-year).

Uncertainty in the model will be investigated by one-way sensitivity analysis and probabilistic sensitivity analysis. One-way sensitivity analysis will be used to test the robustness of the results for (methodological) uncertainties (e.g. discount rate and health-related quality of life instrument used). Parameter uncertainty will be further tested using probabilistic sensitivity analysis. Distributions will be fitted for all parameters in the model, except fixed parameters. Beta distributions will be fitted for probabilities and gamma distributions will be fitted for costs. Net monetary benefits (NMB) will be calculated for each strategy and cost-effectiveness acceptability curves (CEACs) will be constructed. CEACs provide a graphical representation of the probability that a strategy is cost-effective for a range of ceiling ratios. Subsequently, the cost-effectiveness acceptability frontier (CEAF) will be established, to indicate the preferred strategy.

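### The twin-registry sample for ages 5 to 18 is selected at age 18, so it is conditioned on survival: it cannot inform mortality and may understate costs and morbidity

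*Protocol article*

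**What the plan says.** The section on data estimation up to the 18th year of life builds the projection for the reduced sample on three printed sources:

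- the study's own data to age five;
- "parent estimations by means of a questionnaire";
- "a matched sample (n = 250) of 18-year old twin children, of whom NTR data referring to the past will be studied", from the Netherlands Twin Registry (NTR).

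The NTR children are to be "chosen such that their past health at five years of age matches with the health status of the children of the reduced sample". The section then adds a fallback: "If empirical data are missing, data will be obtained by means of literature and/or expert opinion". The Design section describes the model inputs more broadly as "empirically collected data up to five years of life, existing databases, literature and expert opinion".

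The study's own cohort is compared "with respect to mortality, health outcomes, HRQoL and costs from birth up to five years of life", so its mortality data stop at five. The economic result runs to 18 years and is "expressed as the additional costs per life year gained and the additional costs per QALY". The section on empirical data analysis states that QALYs combine mortality with quality of life. The structure of the prognostic model is open: "the final decision regarding which modelling method to use will be made after data become available".

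**The concern.** Eligibility is set at the end of the period of interest and matching at its start. The years in between are then used as a prognosis for children who are about five now. This conditions on the future. Matching at five does not repair it: among children with the same health at five, only those who lived to 18 can be chosen.

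Two things follow. The sample cannot supply a probability of death between 5 and 18, which both the life-year and the QALY results need. Its costs and morbidity also omit the course of the children who died, who are plausibly among the sickest at five. Of the printed sources, this is the only one with observed data for ages 5 to 18; the others stop at five or are parents' expectations.

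The one selection-bias check in the article compares perinatal-registry data of study children with and without missing data. It does not reach the NTR sample.

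**Working it through.** **The plan's own figures.** The 250 has no stated derivation and cannot be reproduced. The reduced sample to which it is matched can be:

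- Full sample after 5% loss: 3,789 × 0.95 = 3,600 singletons; 1,020 × 2 × 0.95 = 1,938 twin children.
- With health problems, after 10% loss: 3,600 × 0.04 × 0.9 = 130 singletons; 1,938 × 0.125 × 0.9 = 218 twin children.
- Without health problems: 56 / 0.8 = 70 per group.
- Total: 130 + 70 = 200 singletons and 218 + 70 = 288 twin children, 488 in all, as stated.

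By design, 348 of the 488 (71%) had resolved or persistent problems in the first year. The NTR sample is thus matched to a group enriched for illness, where conditioning on survival is likely to matter more than in unselected children.

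**What selection at 18 removes.** Let q be the probability of death between 5 and 18. The article gives no value, so 0.1% to 5% is assumed for illustration. Expected deaths in 250 children followed forward from five are 250 × q. With deaths spread evenly over the 13 years, life years lost per child are q × 13 / 2, undiscounted. The last column divides this by the true life years, 13 − 6.5q.

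| Assumed q | Expected deaths, forward cohort | Deaths possible in the planned sample | Life years overstated per child if zero mortality were carried forward | Overstatement |
|---|---|---|---|---|
| 0.1% | 0.25 | 0 | 0.0065 | 0.05% |
| 0.5% | 1.25 | 0 | 0.0325 | 0.25% |
| 1% | 2.5 | 0 | 0.065 | 0.5% |
| 2% | 5 | 0 | 0.13 | 1.0% |
| 5% | 12.5 | 0 | 0.325 | 2.6% |

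The third column is the point: it is 0 for every q. If the 0 out of 250 were read as forward data, it would give a one-sided 95% upper limit of 1 − 0.05^(1/250) = 1.2%. That limit would be spurious, because the sample could not have shown a death.

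**Twin-singleton contrast, as a rough gauge only.** Suppose q applies just to children with health problems, at the stated 12.5% and 4.0%. The difference in life years lost is then (0.125 − 0.04) × q × 6.5: 0.0006 at 0.1%, 0.0055 at 1% and 0.028 at 5%. The last two are 0.04% and 0.21% of 13 years. The two percentages cover resolved and persistent problems together, so the share to which a raised death rate would apply is not known.

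**Costs and morbidity.** No figure can be given. The article has no data on the costs or health course of children who die between 5 and 18.

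**The case against.** The strongest reply is that the article never says the NTR sample supplies mortality. Literature, expert opinion and existing databases are allowed as inputs. A sample without deaths could count as missing mortality data, which is what the fallback is for. Probabilities are to receive beta distributions, and the model is not yet built. The printed list of sources also jumps from item 2 to item 4, so one may have dropped out of the text. This stands against a reading that a reader might infer, namely that modelled mortality from 5 to 18 is zero by construction. The zero belongs to the registry sample, not to the model.

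A reader might also infer that families who left the registry are excluded. The text does not require participation at 18, and a family that left could still have past records. That is a possible further bias to check, not an established one.

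Third, the life-year effect is small. Even the upper contrast above, doubled for a twin pair (2 × 0.028, about 0.055), is about 0.3% of the 18 life years a second child can contribute, before the planned discounting.

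The reply leaves two gaps. The fallback applies only when empirical data are missing, and complete survivor records need not look missing, so nothing ensures that it is used for mortality. A literature death rate also leaves survivor-only costs and morbidity uncorrected.

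**Conclusion.** The selection rule is a real weakness of moderate severity. The NTR sample is conditioned on survival to 18, so it cannot inform mortality between 5 and 18 and may understate costs and morbidity for children with severe problems at five. No source for mortality at those ages is named.

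The size cannot be fixed from the article. The 0.25 to 12.5 missing deaths rest on an assumed q of 0.1% to 5%, and the life-year figures also assume evenly spread deaths and no discounting. The effect on life years is probably small; that on costs and morbidity is unknown.

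A reader might go on to infer that the error favours twins, and so double embryo transfer. That would follow if deaths were concentrated among children with health problems, but the article does not show this, and no change in the ranking of strategies is demonstrated.

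**What to change.** Define the NTR sample at age five. Take twins from the relevant birth years who have an age-five record, match on that record, and follow them forward to 18 with deaths as events and leavers as censored. Compare the age-five health of leavers with that of stayers, since censoring related to health would itself bias the result.

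If the registry does not record deaths, name a separate source for mortality from 5 to 18 by health state, enter it with a distribution so that it takes part in the probabilistic and value-of-information analyses, and state that registry costs and morbidity are conditional on survival to 18.

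The cost is mainly a different selection query in the same registry and, in the second case, one more set of parameters. The planned matching already presupposes age-five records; whether deaths are recorded has to be asked. The downside is that some matched children will have incomplete records to 18. The choice should be settled before the sample is drawn.

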### Outcome measures

Outcome measures are:

1. Health outcomes of the singleton and twin children, such as (perinatal) mortality, morbidity, perinatal outcomes (birth weight, prematurity, APGAR), malformations, developmental problems (psychomotor, cognitive and growth) and behavioural outcomes.

2. Health related quality of life of the singleton and twin children. HRQoL will be measured via proxy ratings by (one of) the parents by means of the EuroQol (EQ-5D) and the Health Utilities Index (HUI3). The EuroQol provides a simple descriptive profile, combining scores on mobility, self-care, daily activities, pain/discomfort and depression/anxiety into a single index value for health status and a VAS scale (0-100). Utility scores for the health states will be calculated by using the UK-tariff [55] and by using the Dutch EQ-5D tariff [56]. The reliability and validity of the EQ-5D has been established [57]. The proxy version of the EQ-5D has good construct validity and convergent validity [58]. The HUI3 will also be used as some studies have reported problems regarding speech development and cognitive problems. The HUI3 is a generic measure consisting of eight attributes (vision, hearing, speech, ambulation, dexterity, emotion, cognition and pain). Each attribute has five or six levels and 972,000 possible health states can be defined. The HUI3 has a multiplicative scoring function which was derived from the Standard Gamble (SG) and Visual Analogue Scale (VAS) in a random sample of the Canadian general population, resulting in possible utility scores ranging from -0.36 to 1.00 [59].

3. (Societal) costs, including resources consumed within the health care sector, such as NICU admissions, hospital admissions, diagnostics, treatments, surgical interventions, and special needs (e.g. physiotherapy, occupational therapy or speech therapy); resources consumed outside the health care sector, such as support, special education, school absence and institutional care; patient and family costs, such as out-of-pocket expenses, travel costs and time costs; and productivity costs.

### Data analysis

#### Empirical data

Health outcomes of the singleton and twin children, including mortality, perinatal outcomes, morbidity and developmental and behavioural problems will be analysed. Subsequently, health outcomes will be expressed in QALYs. QALYs will be calculated based on mortality and HRQoL data retrieved from both the EQ-5D and the HUI. Costs will be calculated by multiplying volumes of resource use with the cost price. Cost prices will be obtained from the Dutch manual of costing studies [60] and financial departments of the participating centres. For cost prices that are not readily available, such as institutional care, special education and school absence, cost price calculations will be performed.

Descriptive statistics will be used to describe the main characteristics and outcomes of IVF singleton and twin children. The base sample and the reduced sample are not representative of the Dutch IVF population as a consequence of the risk stratification and the random selection of subsamples of healthy children. Therefore, before analysing the data, the proportions of high, moderate and low risk singletons and twin children will be adjusted, to properly reflect the ratios in the original population.

Results will be presented with and without stratification for maternal age and parity. The issue of selection (information) bias will be investigated explicitly by comparing PRN data of children with (completely) missing data with PRN data of children included in the analysis.

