### Participants

The study population consists of twins and singletons born from IVF between 2003 and 2005, of whom parents have received IVF treatment in one of the five participating IVF centres in the Netherlands (Academic Medical Centre, Maastricht University Medical Centre, Radboud University Nijmegen Medical Centre, Erasmus Medical Centre and University Medical Center Utrecht). In the Netherlands, subfertility care is well-organized and centred in thirteen licensed clinics [52]. Hospitals without a licence can initiate and monitor the stimulation phase and refer to a licensed hospital for both oocyte retrieval and embryo transfer (satellite clinics) or for embryo transfer alone (transport clinics). Five of the 13 licensed centres and their collaborating transport- and satellite clinics, participate in the TwinSing study.

The *full sample *consists of all IVF twins and IVF singletons born between 2003 and 2005 of whom parents have received treatment in one of the participating centres. A total of 4,809 ongoing pregnancies were reported by these IVF centres between 2003 and 2005, of which - 3,789 singleton and 1,020 twin pregnancies. The actual size of the full sample will be somewhat lower since the reported figures are indicative; they are based on ongoing pregnancies not live births. Inclusion of an older cohort of IVF children is not considered to be valid, since the quality and results of IVF, neonatal and paediatric care have improved considerably during the last decade and since this study relies heavily on retrospective data collection, both from existing registries as well as from parents.

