**Figure 1 F1:**
[figure not shown]
**Risk stratification and sample size (figures are indicative)**.

In order to sufficiently take account of heterogeneity within the children who experienced health problems, it is expected that costs and outcome data of at least 100 singletons and 100 twin children with health problems are required in the reduced sample. Regarding children without health problems, data of 50 singletons and 50 twin children is expected to be sufficient, as variance will be considerably lower. Taking sufficiently account of missing data in all phases of data collection (5% for risk stratification, 10% for data collection up to one year of life and 20% for data collection up to five years of life), a sample size of 175 twin children with health problems, 56 twin children without health problems, 104 singletons with health problems, and 56 singletons without health problems, is required for the reduced sample.

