#### Risk stratification

Risk stratification will be applied to all children in the full sample. Based on information from the PRN regarding the pregnancy (weeks gestation) and the newborn (birth weight, Apgar score and congenital malformations), the children of the full sample will be assigned to a risk profile (i.e. 'low risk', 'moderate risk' or 'high risk'). The risk stratification criteria are: 1) prematurity (< 37 weeks gestation); 2) 5-minute Apgar score (< 7); 3) congenital malformations; and 4) birth weight (< 2,000 gram) (see figure 1). The criteria are set such that the probability of a false negative, i.e. the chance that a child 'at risk' is assigned to the low risk category, is minimized. A child will be assigned to the 'moderate risk' category if the child is born before 37 weeks gestation, has a Apgar score below seven, or has a congenital malformation. If the child also has a birth weight below 2,000 gram, the child will be assigned to the 'high risk' category. The other children will be assigned to the 'low risk' category. Based on figures reported by the PRN [12] and expert opinion it is expected that approximately 8% of the singletons will be assigned to the 'moderate risk' or 'high risk' category. All 'moderate risk' and 'high risk' singletons and a random selection of 10% of the remaining ('low risk') singletons will be included in the base sample. Based on figures reported by the PRN [12] and expert opinion it is expected that half of the twin children is born before 37 weeks gestation, have a low APGAR score or a congenital malformation. Approximately 40% of these twin children will also have a low birth weight (20% of all twin children) and will be assigned to the 'high risk' category. The other 60% of these twin children will have a birth weight above 2000 gram (30% of all twin children) and will be assigned to the 'moderate risk' category [12]. All other children (50% of all twin children) will be assigned to the 'low risk' category. All twin children of the 'high risk' category, a random selection of 30% of the 'moderate risk' category and a random selection of 10% of the 'low risk' category will be included in the base sample.

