#### Empirical data collection from the first year of life up to the fifth year of life

Based on empirical collected costs and outcome data up to the first year of life, a subgroup of children will be selected for data collection up to the fifth year of life, referred to as the reduced sample. All children with resolved or persistent health problems, and a random sample of children without resolved or persistent health problems will be included in the reduced sample. Assuming that missing data are completely at random, resolved and persistent health problems are expected in 4.0% of the singletons and in 12.5% of the twin children. Approximately 488 children will be included in the reduced sample (see figure 1). Besides the data sources mentioned above, cost and outcome data up to the fifth year of life will also be gathered by means of a parent questionnaire. The questionnaire will consist of three parts, the first part referring to the past, the second part referring to the present and the third part referring to expectations regarding the future. The parent questionnaire will focus on health outcomes, HRQoL and costs.

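### The re-weighting rule restores only the risk-category mix, so five-year results from the reduced sample would over-represent children with first-year health problems

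*Protocol article*

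**What the plan says.** The protocol article describes two successive selections.

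- **Phase 1 (Risk stratification).** All moderate- and high-risk singletons enter the base sample, and "a random selection of 10% of the remaining ('low risk') singletons will be included in the base sample". Twin children enter if they are high risk, together with "a random selection of 30% of the 'moderate risk' category and a random selection of 10% of the 'low risk' category". The base sample supplies the first-year data.
- **Phase 2 (Empirical data collection from the first year of life up to the fifth year of life).** The reduced sample consists of "All children with resolved or persistent health problems, and a random sample of children without resolved or persistent health problems". It supplies the five-year data and is the basis for estimation to 18 years.

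Under Data analysis, Empirical data, the article says that neither sample represents the Dutch IVF population, and it gives two reasons: the stratification by risk, and the taking of only subsamples of healthy children. The remedy that follows, to be applied before any analysis, is that "the proportions of high, moderate and low risk singletons and twin children will be adjusted, to properly reflect the ratios in the original population". No adjustment for health-problem status is stated there or elsewhere.

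**The concern.** Two selections are named and one is corrected. Weights on risk category fix the shares between categories; they cannot change the mix of problem and well children within a category. Risk category does not stand in for health status on the plan's own figures: 8% of singletons are expected to be at moderate or high risk but 4.0% to have problems, and 20% of twin children to be high risk but 12.5% to have problems. The at-risk strata therefore hold many well children, and phase 2 discards most of them while keeping every problem child.

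At stake are the five-year parts of research questions 1 and 2 (health outcomes and costs), which come straight from the reduced sample, and any input to the long-term comparison of single and double embryo transfer that is taken from it. The inflation differs between singletons and twin children, so the contrast is distorted as well as the levels.

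**Working it through.** **Inputs.** Participants: "3,789 singleton and 1,020 twin pregnancies", hence 2,040 twin children. Losses, from the sample-size text after Figure 1: "5% for risk stratification, 10% for data collection up to one year of life and 20% for data collection up to five years of life". Risk shares, from Risk stratification: "approximately 8% of the singletons will be assigned to the 'moderate risk' or 'high risk' category"; twin children 20% high, 30% moderate, 50% low. Expected problems: 4.0% of singletons, 12.5% of twin children.

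**Reproducing the plan's counts.**

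- Singletons: 3,789 × 0.95 = 3,600. Base sample 0.08 × 3,600 + 0.10 × 0.92 × 3,600 = 288 + 331 = 619.
- Twin children: 2,040 × 0.95 = 1,938. Base sample 0.20 × 1,938 + 0.30 × 0.30 × 1,938 + 0.10 × 0.50 × 1,938 = 388 + 174 + 97 = 659. Total 1,278, as stated.
- With problems and first-year data: 3,600 × 0.04 × 0.90 = 129.6 singletons; 1,938 × 0.125 × 0.90 = 218.0 twin children.
- Without problems: 56 / 0.80 = 70 in each group.
- Reduced sample: 130 + 70 = 200 and 218 + 70 = 288, total 488, as stated. After 20% loss the problem children number 103.7 and 174.4, against the printed 104 and 175.

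The counts of 130 and 218 carry no phase-1 sampling fraction. They arise only if essentially all problem children lie in the fully sampled strata: at-risk singletons and high-risk twin children. That is the case worked below.

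**Phase-2 fraction for well children.** Children with first-year data (90% of the base sample): singletons 259.2 at risk and 298.0 low risk, total 557.2; twin children 348.8 high, 157.0 moderate and 87.2 low, total 593.0.

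- Singletons: 70 / (557.2 − 129.6) = 0.164
- Twin children: 70 / (593.0 − 218.0) = 0.187

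The fraction for problem children is 1 in both groups.

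**Risk-only weighting, as written.** Estimated prevalence = Σ (population share of stratum) × (problem share of that stratum in the reduced sample).

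| | Problem | Well kept | Problem share | Weighted estimate | Plan's prevalence |
|---|---|---|---|---|---|
| At-risk singletons | 129.6 | 129.6 × 0.164 = 21.2 | 0.859 | 0.08 × 0.859 = 6.9% | 4.0% |
| High-risk twin children | 218.0 | 130.8 × 0.187 = 24.4 | 0.899 | 0.20 × 0.899 = 18.0% | 12.5% |

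The inflation is 1.72-fold and 1.44-fold. The gap is 18.0 − 6.9 = 11.1 points against 12.5 − 4.0 = 8.5, a ratio of 1.3. If a problem child costs the same in both groups, and a well child likewise, the cost difference is overstated by the same 1.3 whatever those costs are.

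**Weighting by both phases.**

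- Singletons: 129.6 / (129.6 + 21.2/0.164 + 48.8/(0.10 × 0.164)) = 129.6 / 3,240 = 4.0%.
- Twin children: 218.0 / (218.0 + 130.8 + 157.0/0.30 + 87.2/0.10) = 218.0 / 1,744 = 12.5%.

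**Sensitivity.** For a stratum with problem rate q and phase-2 fraction f, the reduced-sample share is q / (q + f(1 − q)). This exceeds q whenever 0 < q < 1 and f < 1, so the levels can only move up.

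- The text gives no split of at-risk singletons into moderate and high, so they are treated as one stratum. Unequal rates would lower the 6.9%. With two equal halves at rates of 75% and 25% (an assumption), it is 0.04 × (0.948 + 0.671) = 6.5%. It reaches 4.0% only if one category held problem children alone and the other none.
- With 10%, 25% or 50% of singleton problems in the low-risk group, the estimate is 9.2%, 12.5% or 17.9%. With twin problems split high/moderate/low as 80/20/0, 70/20/10 or 50/30/20, it is 27%, 34% or 42%. These splits give fewer problem children than the planned 130 and 218.

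**The case against.** The best defence is that the article recognises both selections, states the aim of reflecting the original population, and condenses a fuller document in which weight formulas would normally sit. The intent is clear, and it would be unfair to say that the authors overlooked the second selection. But the sentence does more than omit detail. It says which proportions will be restored, and for the reduced sample those do not achieve the stated aim. The comparison of registry data in the same section addresses missing data, not this selection.

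Three stronger readings are tempting and are not supported.

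- **That all 5-year and 18-year estimates are tilted.** Development TwinSing model leaves the structure open and expects a Markov model. If its states separate children with and without problems, phase 2 selects on the conditioning variable, and the starting mix could come from the base sample, where risk weights are correct. Such a model could avoid part of the bias. The article neither commits to this route nor excludes it, and it would not rescue five-year means reported directly.
- **That the contrast could be overstated about three-fold.** A 25% problem rate in both high- and moderate-risk twin children gives 34.5% and a gap ratio of (34.5 − 6.9) / 8.5 = 3.2. It also gives only 0.25 × (348.8 + 157.0) = 126 problem twin children, not 218.
- **That problem children are over-represented six-fold in every risk category.** The ratio of sampling fractions is 1/0.164 = 6.1 for singletons and 1/0.187 = 5.3 for twin children. In the case that fits the counts, low-risk children and moderate-risk twin children have no problems to over-represent, and the problem share in at-risk singletons rises from 50% to 86%, or 1.7-fold.

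**Conclusion.** The rule is wrong as written for the reduced sample. If it is followed, five-year empirical results, and any model input taken directly from them, over-represent children with first-year problems. The size found above rests on four assumptions: the plan's expected rates, problems confined to at-risk singletons and high-risk twin children, a common problem rate across at-risk singletons, and a phase-2 sample of well children that is simple random within singletons and within twin children.

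The upward direction of the levels does not depend on where the problems fall. The direction of bias in the contrast does: with half of singleton problems in the low-risk group and all twin problems in the high-risk group, the gap would be 18.0 − 17.9 = 0.1 points, so it would shrink. That split does not match the plan's singleton count, but it shows that a 1.3-fold overstatement cannot be assumed once data arrive.

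One-year base-sample results are not affected. The effect on 18-year results depends on a modelling choice not yet made.

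**What to change.** Replace the single adjustment sentence with one rule per sample.

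- **Base-sample (one-year) results:** weight by the inverse phase-1 fraction, by risk stratum and by singleton or twin.
- **Every reduced-sample result, including model inputs taken from it:** weight by the product of that inverse and the inverse phase-2 fraction. The phase-2 fraction is defined by health-problem status and by singleton or twin, and also by risk stratum if the phase-2 draw is stratified by it.
- **Standard errors:** use variances that reflect the two-phase design.

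The cost is a change of wording. The fractions are fixed by the sampling and need only be recorded; no data are added. The weights will be uneven: a low-risk well singleton carries 1/(0.10 × 0.164) = 61, against 1 for an at-risk problem child. That loss of precision comes from the design already chosen, and the variance should show it.
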